## Abstract

Autism Spectrum Disorder (ASD) affects approximately 1 child in 54, with a 35-fold increase since 1960. Selected studies suggest that part of the recent increase in prevalence is likely attributable to an improved awareness and recognition, and changes in clinical practice or service availability. However, this is not sufficient to explain this epidemiological phenomenon. Research points to a possible link between ASD and intestinal microbiota because many children with ASD display gastro-intestinal problems. Current large-scale datasets of ASD are limited in their ability to provide mechanistic insight into ASD because they are predominantly cross-sectional studies that do not allow evaluation of perspective associations between early life microbiota composition/function and later ASD diagnoses. Here we describe GEMMA (Genome, Environment, Microbiome and Metabolome in Autism), a prospective study supported by the European Commission, that follows at-risk infants from birth to identify potential biomarker predictors of ASD development followed by validation on large multi-omics datasets. The project includes clinical (observational and interventional trials) and pre-clinical studies in humanized murine models (fecal transfer from ASD probands) and in vitro colon models. This will support the progress of a microbiome-wide association study (of human participants) to identify prognostic microbiome signatures and metabolic pathways underlying mechanisms for ASD progression and severity and potential treatment response.

## 1. Introduction

Autism Spectrum Disorder (ASD) is a lifelong neurodevelopmental disorder characterized by deficits in social communication and social interaction, in addition to restricted, repetitive patterns of behavior, interests, or activities [1]. As a spectrum disorder, its symptoms may range from mild to severe. Some children may have strong language and intellectual abilities whereas others may not be verbal and may require lifelong care. Globally, ASD incidence has shown a 35-fold increase compared to the 1960s and 1970s, when the first epidemiological studies were conducted [2,3,4,5,6]. As documented by the Centers for Disease Control and Prevention, ASD affects 1 in 54 children in USA [7] and 1 in 89 in Europe [8].

Children born in a family with an affected sibling show a ten-fold higher risk of developing the condition [9]. These data, including a large-scale exome sequencing study [10], suggest a combination of non-Mendelian genetic and environmental factors in ASD pathogenesis [11,12]. One environmental factor that is emerging as important for ASD risk is the immune system [13,14,15,16]. Indeed, individuals with ASD show increased expression of genes encoding mediators of the innate immune response [15]. Low-grade systemic inflammatory events [17,18], combined with the hypofunction of protective, anti-inflammatory mechanisms [19], lead to mechanisms related to the biochemical and neuroanatomical characteristics associated with autism pathogenesis [20,21,22]. Immunoregulation, in addition to dysregulated immunoregulation, particularly during the first 1000 days of life [23], are guided by the gut microbiome. Low-grade systemic inflammatory responses can lead to psychiatric disorders, such as ASD and psychological stress, which leads to further inflammation through pathways involved in the intestinal microbiota homeostasis [24,25].

Many individuals with ASD have symptoms of associated comorbidities. These include medical comorbidities, such as gastrointestinal (GI) and immune system disorders (namely gut dysbiosis, susceptibility to infections, and increased prevalence of autoimmune disorders), sleep problems, feeding problems and epilepsy; comorbid psychopathology, including Attention-Deficit/Hyperactivity Disorder (AD/HD), anxiety, mood problems, disruptive behavior; and developmental comorbidity, namely the presence of an intellectual disability.

A large number of individuals are living with ASD. Thus, ASD is a serious public health concern. The medical expenditure for ASD is higher than that for cancer, heart disease, and stroke combined [26,27]. Blumberg et al. [28] suggested that the recent increase in prevalence could be in part attributed to greater recognition and awareness, or changes in clinical practice or service availability. However, these changes are not sufficient to explain this phenomenon [6]. ASD is a multifactorial disorder; therefore, the contribution of environmental factors could explain its development in addition to why different therapeutic approaches, based on gene/environment interaction theory, have achieved conflicting results [29,30,31]. The GEMMA (Genome, Environment, Microbiome and Metabolome in Autism) team hypothesizes that many environmental factors can alter intestinal microbiota composition and activity, causing epigenetic modifications, changes in the metabolome profile, and increases in intestinal barrier permeability and macromolecule trafficking with the alteration of immune responses, thus contributing to the progression and development of ASD. Furthermore, it is hypothesized that the genome/metagenome interaction determines the switch from immune tolerance to immune response. Environmental stimuli, including dietary and microbial factors, can trigger an immune response, such as the neuroinflammation responsible for the behavioral changes that characterize ASD and intestinal inflammation causing its GI comorbidity.

The existence of a gut–brain axis was hypothesized by Bolte in the late 1990s [32]. This was one of the first reports of unhealthy changes in the intestinal tract’s resident community (microbiome), driving both behavioral and GI problems in babies with ASD. Finegold et al. [33] showed that the increase in toxin-producing gut bacteria populations directly affects the brain via the vagus nerve. Currently, changes in gut microbiota of ASD patients with and without GI symptoms are well established [34,35,36], suggesting the potential beneficial effect of fecal transplantation [37,38].

Unfortunately, current large-scale studies of ASD are mainly of cross-sectional study design, which can provide information about associations between microbiome changes and ASD diagnoses but lack the information regarding the temporality of these changes. This limits inferences about causality or utility as an early life biomarker. Indeed, currently, there are no established biomarkers for ASD to enable its clinical diagnosis, which relies on behavioral evaluations. In addition, no medications are currently available to treat the core symptoms of ASD and results from intervention research are mixed [39].

## 2. Study Design

GEMMA is a multi-center, prospective, open-label, uncontrolled study with an observational and an interventional arm, comprised of collaborators in the European Union and the United States. It is coordinated by the European Biomedical Research Institute of Salerno (EBRIS), in Campania, Italy. GEMMA aims to study genomic, environmental, microbiome, and metabolomic factors that, via the immune system, may contribute to the development of ASD longitudinally. This study offers the potential to identify the mechanisms and/or biomarkers involved in either development or exacerbation of ASD signs and symptoms, which will potentially broaden the range of available therapeutic interventions (Figure 1).

The project includes clinical (observational and interventional trials) and pre-clinical studies. Several pre-clinical studies in humanized murine models (fecal transfer from ASD probands) and in vitro colon models will be performed simultaneously with clinical studies from the moment of recruitment of at-risk infants and their affected ASD sibling. This will support the progress of a microbiome-wide association study (of human participants) to identify prognostic microbiome signatures and metabolic pathways underlying mechanisms for ASD progression and severity and potential treatment response. The preclinical work will provide valuable information regarding validation of specific biomarkers mechanistically linked to the onset of ASD, which will be used to rationalize future patient stratification for primary intervention.

### 2.1. Pre-Clinical Studies

An in vitro micro-scale colon microbiota model or “colon microcosm” that mimics the microbiota of the human colon will be used to investigate effects of various combinations of prebiotic fiber types and probiotics on microbiota composition and functionality. The colon microcosms will be inoculated with fecal samples collected from children diagnosed with ASD with and without a history of GI problems, and from healthy siblings (controls) between the ages of 3 and 14. Samples will be excluded if the participants have used psychotropic medications in the previous 6 months and antibiotics and/or probiotics in the previous 2 months (Figure 2).

The impact of pre- and probiotic combinations on microbiota composition and function will be measured by 16S rRNA gene sequencing, metagenomics, and targeted and untargeted metabolites analyses.

The preclinical studies in murine models will be carried out simultaneously with the other studies for two reasons: to provide further information on validation of specific biomarkers mechanistically linked to the onset of ASD and, consequently, to treat future patients primarily with a more precise intervention.

The preclinical studies in murine models include the development of humanized mouse models through transplanting fecal samples from a well-characterized ASD diagnosed proband (and sibling controls) in the families included in the clinical observational study. The fecal samples will be the same as those collected for the in vitro studies described above. In addition to wild type naïve mice, fecal transplantation will be conducted in genetically vulnerable (PCDH-KO), food allergic (CMA), and valproate-treated (VPA) male mice which have been previously demonstrated to show ASD-like behavior [40,41,42,43]. The natural gut microbiota of these mice will be depleted before transplantation with the human fecal samples. This will be achieved at the age of 3 weeks, with antibiotic treatment followed by a bowel cleansing according to procedures described by Le Roy and coworkers [44]. Fecal transplantation will also be conducted in germ-free male mice, which have abnormal development of the nervous system and show deficits in cognition, social behavior, and stress-related behaviors [45,46,47,48,49,50,51]. The microbial content of human donors will be orally administered to recipient microbiota-depleted or germ-free mice. Behavior, microbiota composition, gut permeability, metabolites, mucosal and systemic immune profiles (intestinal tract, mesenteric lymph nodes, blood, and spleen), neurotransmitters, and neuroinflammation in the brain will be evaluated to investigate the mechanistic evidence of the intestinal microbiota–brain axis in ASD. In addition, ASD-humanized VPA and CMA male mice will be suitable splenocyte donors for transferring their behavioral phenotype to naïve mice to reveal whether the ASD-like phenotype is microbiome-immune system-dependent. A second series of preclinical studies will establish whether correction of intestinal microbial dysbiosis by pre/pro/synbiotic intervention prevents and/or treats ASD-like behavior in ASD murine models. Selected ASD humanized murine models will be fed diets supplemented with selected pre/pro/synbiotics, which will be prescreened using microcosms systems as described above. Those that affect neurodevelopment, behavior, and the GI tract positively will be used in the clinical intervention trial.

### 2.2. Clinical Study

#### 2.2.1. Participants

GEMMA aims to enroll 600 infants younger than 6 months/26 weeks of age, who have an older sibling with ASD for the observational trial. The recruitment will be carried out in three different centers: Irish Center for Autism and Neurodevelopmental Research (ICAN) at the National University of Ireland, Galway, Azienda Sanitaria Locale Salerno (ASL), and satellite centers in Italy, and Mass General Hospital for Children (MGHFC) Lurie Center for Autism in USA. The first study samples must be collected prior to the introduction of solid foods. Children who have started any other therapeutic intervention for ASD will also be excluded from the study. According to our previous experience with similar projects involving two cohorts of infants at-risk of celiac disease [52,53], enrollment will be performed by inviting parents’ of the autistic patients who are followed by the recruitment clinics to participate in the study in the case of newborns, and advertising the study among ASD support and ASD patients’ groups. Moreover, a traditional and social media diffusion plan was created to increase the project knowledge and support. No compensation will be provided to the participant.

Infants aged 18–36 months who were recruited, completed the observational study, developed clinical signs and symptoms of ASD, and whose parents permit the intervention of solely dietary and oral therapy in this study, will be invited to enroll for a follow-on dietary interventional trial.

#### 2.2.2. Observational Trial

This study phase will evaluate infants at high risk of ASD. To achieve the sample size needed for clinical and biological comparisons, and ensure there is a reasonable representation across study sites, each site will target recruitment of 200 infants at high risk of developing ASD, over a 3 year period. All recruited children will undergo regular clinical and laboratory evaluations for 36 months, or more in the case of ASD development based on the annual intermediate clinical data check. Blood, urine, stools, and saliva samples will be collected every 6 months until 36 months of age.

Regarding GI symptoms, children will be evaluated for chronic irregular bowel movements (constipation, diarrhea), encopresis, recurrent abdominal pain, gastroesophageal reflux, and vomiting or food aversion. On these bases, the evaluable target study population (see Table 1 for inclusion/exclusion criteria) will be divided into four groups (depending on their clinical outcome: neuro competent at-risk infants with (NC-GI) and without GI symptoms (NC), ASD infants with GI symptoms (ASD-GI) and ASD infants without GI symptoms (ASD)). Maternal and paternal genomic samples will be taken from parents of infants at the time of enrollment and analyzed to examine inherited and de novo genetic traits.

Autism Diagnostic Observation Schedule (ADOS Toddler) evaluation [54] will be conducted every 6 months by a trained physician, starting at 12 months of age. For children younger than 24 months who test positive in the ADOS Toddler evaluation, the evaluation will be repeated one month later to confirm diagnosis to enroll the infant in an interventional study, and will be used to divide the participants into two groups: ASD children or non-ASD children (typically developing). Typically developing children will be followed until 36 months (see Figure 3) of age and their data will be selected at the end of the study to provide the information for the matched control comparisons.

Additional behavioral assessments include Early Screening for Autism and Communication Disorders and Repetitive Behavior Scale [55,56], Mullen Scales of Early Learning (MSEL) [57], and Vineland Adaptive Behavior Scales (VABS) [58]. These assessments will take place at 24 and 36 months of age.

#### 2.2.3. Interventional Trial

This prospective, multi-center, open-label, uncontrolled study (Figure 4) evaluates the effects of pre/pro/synbiotics supplementation started in infants between the ages of 18 and 36 months with a diagnosis of ASD.

A minimum of 40 children diagnosed with ASD from the observational trial will be recruited to the interventional trial, subject to parental consent. Each ASD infant will undergo a Positron Emission Tomography (PET) scan of their brain, at the beginning and end of the interventional study, to obtain information on the degree of neuro-inflammation and the potential effect of the intervention. The presence/absence of GI symptoms will also be evaluated.

Clinical and laboratory assessments will be made at the time of enrollment, monthly for 3 months, and then at the conclusion of the 6 month study.

The study was approved by the relevant ethics committee of each enrolling country. In particular: CE Campania Sud (IRB n.30/2019) for Italy; Partners Human Research (IRB ver.01/04/2019) for USA; and Clinical Research Ethics Committee of Galway University Hospital (IRB n. C.A. 2127/19) for Ireland. A written consent form will be signed by each participant or their legal representative. The clinical trial was registered with the access number: NCT04271774 (https://clinicaltrials.gov).

### 2.3. Data Collection

The timetables of data and sample collection are shown in Supplementary Tables S1–S3 and in Figure 3. Pre-screening may occur verbally via a telephone call or in person at a hospital clinic. Parents who wish to enroll their infant in the study will provide proof of ASD diagnosis for the child with the condition. Each clinical site will be responsible for its own data collection and management. Data will be monitored remotely for completeness and coherence by the project management team. All data will be collected through a secure, internet-based electronic capture system (REDCap) [59]. Participating institutions will be granted access to the electronic storage module with all appropriate forms and schedules pre-loaded. Each institution will only be able to view data for participants enrolled at their site. The coordinating center will be granted access to unidentified data from all sites through the electronic data capture system.

#### Parental and Child Questionnaires

An online questionnaire will be filled out by the family every month during the 6 months of intervention. Moreover, it will be filled out by the family at 9, 15, 21, 27, and 33 months of age and will include infant dietary data and the use of concomitant medication (vaccinations and antibiotics), demographics, infant clinical history including but not limited to infections, onset of food intolerance, and chronic stress. Parents will also be requested to complete the Aberrant Behavior Checklist (ABC) at all visits and at 9 months. Assessment scales for infant development (Rome 3 Criteria GSRS, ADOS-Toddler, Mullen scale, CGI-S, CGI-I) will be assessed, during the interventional trial, every month for the first three months of the study, and three months later at the final 6-month study visit.

### 2.4. Serological Markers

#### 2.4.1. Whole Blood

Blood sampling will take place at enrollment, 0–6 months post birth, and at 12, 18, 24, 30, and 36 months of age. Blood for hematology, biochemistry evaluation, biomarker identification, and genetic assays will be collected from infants fasting for at least 3 h. The blood collection procedure is as follows: via umbilical cord for infants enrolled during gestation, or by heel sampling at enrollment (at 0–6 months of at-risk infant age), 1 mL every 6 months from 12 months of age, and finally at development of ASD or at the 36-month (observational study termination visit). The assays that will be performed on blood include whole genome sequencing on infants that develop ASD. Furthermore, DNA methylation (DNAm) will be measured among infants that develop ASD using samples obtained at three time points: (1) enrollment, (2) the time of ASD diagnosis, and (3) the completion of the interventional trial. In preparation for future testing, a biorepository will be established. A blood sample will be taken after 12 months for peripheral blood mononuclear cell (PBMC) isolation and immune profiling analysis.

Moreover, serum testing will take place at enrollment of the clinical study, 0–6 months post birth, and at 12, 18, 24, 30, and 36 months of age. A quantity of 500 uL of serum will be taken from the infant fasting for 3 h to evaluate serum zonulin (20 μL); serum IgA and IgG anti-gliadin and anti-casein antibody determination (40 μL) by the ELISA method; serum pro-inflammatory cytokines, including cIL-1, TNF-α, IFN-, IL-10, IL-12, IL-6, IL15, and IL-8 by Bioplex assay (75 μL) [60]; and cytokine gene expression by RT-PCR.

If ASD is developed, whole genome sequencing of the infant and of both parents will be performed.

#### 2.4.2. Stool, Urine, and Saliva Samples

Every 3 months after enrollment, urine and stool samples will be collected at home and shipped to the laboratory for biomarker assay. Because patient samples are divided according to the presence and absence of a history of GI problems with an onset earlier than the initiation of toilet training, the aim is to select children with a biological rather than psychological etiology of GI discomfort. The control group includes fecal samples from age- and gender-matched control participants without previous diagnosis of a neurodevelopmental disorder and without a history of GI problems. Exclusion criteria for the use of patients and control samples include the use of psychotropic medication for the previous 6 months and antibiotics and/or probiotics for the previous 2 months.

Saliva samples will be taken for microbiome and glycome (the whole set of carbohydrates) analysis. Moreover, when possible subsequent analysis/correlation with blood biomarker levels either within this protocol or at a later timepoint will be performed. The saliva samples will be analyzed for pro-inflammatory markers and for six inflammatory markers selected from a previous study [61].

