### 4.2. Power Analysis

We estimated a conservative drop-off of 20% based on our previous experience with similar projects involving two cohorts of infants at-risk of celiac disease, one that has been followed for 10 years with a 20% drop-off [52] and a second that has been followed up to 7 years with a 12% drop-off [53]. The final cohort will comprise approximately 500 at-risk infants. Expected prevalence of ASD at 18–24 months in first-degree relatives is 14.7% [9], so in this study we estimate 73 ASD diagnoses. The expected prevalence of GI symptoms in an ASD population is 60% [80], so we anticipate 44 of the 73 ASD diagnosed infants to also present GI symptoms.

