**Figure 2 brainsci-10-00743-f002:**
[figure not shown]
Preclinical studies—development of humanized mouse models by transplanting fecal samples from a well-characterized ASD diagnosed proband (and sibling controls). Four groups of children, each with 4 children, recruited in one center in Europe (Italy): autistic with no GI problems, autistic with GI problems, controls without or with GI problems. Ongoing.

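### The stool-control definition excludes children with GI problems, which contradicts the article's four-group designs and leaves ASD-GI without a GI-matched comparator

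*Protocol article*

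**What the plan says.** All references are to the protocol article.

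- **Section 2.4.2 (Stool, Urine, and Saliva Samples).** On the patient side both GI strata are kept: "patient samples are divided according to the presence and absence of a history of GI problems". The control group is described as age- and gender-matched "control participants without previous diagnosis of a neurodevelopmental disorder and without a history of GI problems". The section describes no other stool control.
- **Section 2.2.2 (Observational Trial).** The cohort is divided into four groups by ASD and GI status. The non-ASD half is "neuro competent at-risk infants with (NC-GI) and without GI symptoms (NC"). On typically developing children, the same section says "their data will be selected at the end of the study to provide the information for the matched control comparisons", with no restriction on GI history.
- **Figure 2 (preclinical fecal donors).** There are four groups of four children: "autistic with no GI problems, autistic with GI problems, controls without or with GI problems".
- **Section 4.2 (Power Analysis).** About 500 infants remain. 73 ASD diagnoses are expected, and 44 of those children are expected to have GI symptoms (60%).

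**The concern.** Sections 2.2.2 and Figure 2 each set out a two-by-two layout of ASD by GI status. The control rule in Section 2.4.2 empties one of the four cells, the non-ASD children with GI problems, while both ASD cells stay filled.

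The study aims to find microbiome signatures of ASD, and GI symptoms are a plausible rival explanation for a difference in stool. With the NC-GI cell empty, the larger ASD subgroup can be compared only with children who differ from it in both ASD and GI status. A stool feature linked only to GI symptoms could then look like an ASD feature in any contrast that includes ASD-GI. The FDR adjustment in Section 4.1 does not help, because it handles multiplicity and not a systematic shift caused by how controls were chosen.

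**Working it through.** **Inputs from the article.** 600 infants enrolled (Section 2.2.1). Drop-off 20%, final cohort about 500, ASD prevalence 14.7%, GI symptoms in 60% of ASD (Section 4.2). Significance level 0.05 (Section 4.1; two-sided assumed).

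**Assumptions, because the article gives no figure.** GI effect on a stool feature, δ: 0.5 SD, range 0.3 to 0.8. Natural GI share among non-ASD infants, g: 10% to 40%. SD of 1 in every group.

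**1. The article's own counts.** 500 × 0.147 = 73.5 (stated 73). 73 × 0.60 = 43.8 (stated 44). That leaves 73 − 44 = 29 ASD infants without GI symptoms and 500 − 73 = 427 non-ASD infants. Taking the 20% drop-off literally, 600 × 0.80 = 480 and 480 × 0.147 = 70.6, so 71 cases. I use 71 for the main illustration and show 73 beside it.

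**2. What each contrast estimates.** Let α be the ASD effect, δ the GI effect and γ their interaction.

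| Contrast | Estimates | Available under Section 2.4.2? |
|---|---|---|
| ASD − NC | α | yes |
| ASD-GI − ASD | δ + γ | yes |
| ASD-GI − NC | α + δ + γ | yes |
| ASD-GI − NC-GI | α + γ | no |
| (ASD-GI − ASD) − (NC-GI − NC) | γ | no |

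ASD without GI against GI-free controls has no GI bias. If γ = 0, both α and δ can be estimated from the three remaining groups. What is lost is γ and the GI-matched comparison for ASD-GI.

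**3. A pooled contrast.** All ASD against GI-free controls estimates α + 0.60(δ + γ). With α = γ = 0 the apparent ASD effect is 0.60 × δ = 0.60 × 0.5 = 0.30 SD.

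**4. How often that would be declared.** P = Φ(d / √(1/n₁ + 1/n₂) − 1.96), unadjusted.

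- 71 vs 71, d = 0.30: 0.30 / √(2/71) = 1.79, so P = 43%. With 73 vs 73, P = 44%.
- 71 vs 71, δ = 0.3 (d = 0.18): 19%. δ = 0.8 (d = 0.48): 82%.
- 73 vs every GI-free non-ASD infant, 427 × (1 − g) = 384 down to 256, d = 0.30: 65% down to 62%.

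**5. Removing the restriction and nothing else.** The bias of the pooled contrast becomes (0.60 − g) × δ. For δ = 0.5 that is 0.25 SD at g = 10% and 0.10 SD at g = 40%. With 73 vs 427, P = 51% and 12%. The bias shrinks but remains. Within a GI stratum it is zero.

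**6. If the sentence governs the donors.** Figure 2 has 4 + 4 ASD donors, a GI share of 4/8 = 50%. The restriction would remove the cell of four controls with GI problems, and a pooled contrast would carry 0.50 × δ. The percentages in step 4 do not carry over to groups of four.

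**The case against.** **The sentence may not describe the cohort.** Its medication exclusions match those for the donor samples in Section 2.1, and the toilet-training wording suits children aged 3 to 14 better than infants enrolled before 6 months. This is a fair point. The opening of Section 2.4.2, on three-monthly home collection after enrolment, points the other way. The contradiction stands on either reading: with Section 2.2.2 for the cohort, with Figure 2 for the donors. The cohort-scale figures apply only on the first reading.

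**The group is said to include such controls, which need not be exclusive.** No other stool control is described there, so the sentence reads as the control rule. If GI-positive controls are intended, the text still has to say so.

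**ASD and GI effects can still be separated.** A reader might infer that under this rule no ASD signature can be told apart from a GI signature. The article does not support that. Patient samples are divided by GI history, ASD without GI against GI-free controls is clean, and an additive model identifies both main effects. This objection stands and limits the point to ASD-GI, the interaction and any pooled contrast.

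**The false-positive rates assume an analysis the article does not state.** This also stands. Section 2.2.2 does form two groups, ASD and non-ASD, but no section specifies a pooled, GI-unadjusted stool contrast. The GI effect sizes are assumed and the rates are before FDR adjustment.

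**GI symptoms may not be a confounder.** The Introduction hypothesises an immune response, triggered in part by microbial factors, with intestinal inflammation behind the GI comorbidity. GI symptoms may thus lie downstream of the microbiome, and adjusting for them could remove part of the effect of interest. This bears on how the adjusted analysis is ranked. It does not justify leaving NC-GI empty.

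**Conclusion.** The contradiction is textual and rests on no assumption: the control rule in Section 2.4.2 conflicts with Section 2.2.2 or with Figure 2, depending on which samples it governs.

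If it governs the cohort and is followed, about 44 of 73 expected ASD cases have no GI-matched comparator and the ASD-by-GI interaction is not estimable. These two losses hold whatever the GI effect is. The 0.60 × δ bias is conditional on a pooled contrast without GI adjustment. The 0.30 SD and 43% figures further assume a GI effect of 0.5 SD, no ASD effect, no interaction and unadjusted two-sided testing at 0.05. They show the scale of the problem and do not predict the study's error rate. Nor should the whole excess over 5% be charged to the restriction, since unrestricted controls would still leave part of it in a pooled contrast.

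**What to change.** 1. State in Section 2.4.2 which samples the control definition governs: the observational cohort, the preclinical donors, or both.
2. Delete the final condition of that definition, the one on GI history, so that GI-positive controls are included as in Section 2.2.2 and Figure 2.
3. Make the stool contrasts within GI strata: ASD-GI against NC-GI, and ASD against NC. Step 2 alone only reduces the bias of a pooled contrast.
4. Report a GI-adjusted overall ASD effect as secondary, given the article's own hypothesis about GI symptoms. The stratum contrasts also condition on GI status, so they should be read as ASD differences at a given GI status, which is what the four-group layout sets out to compare.

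**Cost.** No new recruitment or sampling. Section 2.2.2 already assesses GI symptoms and collects stool in all infants, and selects controls only at the end of the study; Figure 2 already lists donor controls with GI problems. The price is precision. In SD units, the standard error √(1/n₁ + 1/n₂) is 0.13 for 73 vs 427. For ASD-GI against NC-GI it is 0.21 at g = 10% (44 vs 43) and 0.17 at g = 40% (44 vs 171). For ASD against NC it is 0.19 (29 vs 384) to 0.20 (29 vs 256).
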